## **8 Adverse Events (AE) and Serious Adverse Events (SAE)**

The investigator will be responsible for the detection and documentation of events meeting the criteria and definition of an adverse event (AE) or a serious adverse event (SAE) as provided in section 8.1. During the study, when there is a safety evaluation, the investigator or delegated research staff will be responsible for detecting AEs and SAEs, as detailed in this section of the protocol.

### **8.1 Definition of an Adverse Event (AE)**

Any untoward medical occurrence in a participant or clinical investigation participant, temporarily associated with the use of a medicinal product, whether or not considered related to the medicinal product.

For the current study, an AE is defined as any unfavourable and unintended sign (including an abnormal laboratory finding), symptom, or disease (new or exacerbated) temporally associated with the use of a medicinal product, whether or not considered related to the medicinal product.

Examples of an AE **include**:

- Exacerbation of a chronic or intermittent pre-existing condition including either an increase in frequency and/or intensity of the condition.
- New conditions detected or diagnosed after investigational product administration even though it may have been present prior to the start of the study.
- Signs, symptoms, or the clinical sequelae of a suspected interaction.
- Signs, symptoms, or the clinical sequelae of a suspected overdose of either investigational product or a concurrent medication (overdose *per se* should not be reported as an AE/SAE).
- Acute episode of psychosis

Examples of an AE **do not include** a/an:

- Medical or surgical procedure (e.g. endoscopy, appendectomy); the condition that leads to the procedure is an AE.
- Situations where an untoward medical occurrence did not occur (social and/or convenience admission to hospital).

In this study, AEs may include the following documented side effects: Anorexia, vomiting, allergic reactions

## **8.2 Definition of a Serious Adverse Event (SAE)**

A serious adverse event is any untoward medical occurrence that, at any dose:

- a) results in death
- b) is life threatening
- c) requires hospitalisation or prolongation of an existing hospitalisation.  
*Hospitalisation for elective treatment of a pre-existing condition that did not worsen from baseline is not considered an AE.*
- d) results in disability/incapacity, or
- e) is a congenital abnormality / birth defect.
- f) Any event deemed by the investigator as being a significant medical event.

## **8.3 Time Period, Frequency, and Method of Detecting AEs and SAEs**

All adverse events will be recorded between the time of consent and the final visit (week 14), two weeks post final treatment. Each Participant will be monitored regularly by the investigator and study personnel for adverse events occurring throughout the study. The research assistant will enquire about AEs by asking the following non-leading questions:

At the first scheduled visit (pre-dosing) participants will be asked:

*"How are you feeling?"*

At subsequent scheduled visits, participants will be asked:

*"Since your last visit, have you had any health problems?"*

## 8.4 Recording of AEs and SAEs

When an AE/SAE occurs, the investigator or delegate will review all documentation (e.g. hospital progress notes, laboratory, and diagnostic reports) relative to the event. The investigator or delegate will then record all relevant information regarding an AE/SAE in to the CRF.

For each adverse event, start and stop dates, action taken, outcome, intensity (see Section 8.7.1) and relationship to study product (causality) (see Section 8.7.2) will be documented. If an AE changes in frequency or intensity during a study, a new entry of the event will be made in the CRF. All details of any treatments initiated including concomitant medications due to the adverse event will be recorded in the Case Report Form (CRF).

## 8.5 Prompt Reporting of SAEs

Once an investigator becomes aware that an SAE has occurred in a study Participant, he/she will immediately notify the University of Queensland (sponsor) by contacting the study monitor via telephone to notify him/her of the event. The SAE form must be completed as thoroughly as possible with all available details of the event, signed by the investigator (or appropriately qualified designee), and faxed to the study monitor within 24 hours of first becoming aware of the event.

If the investigator does not have all information regarding an SAE, **he/she will not wait to receive additional information before notifying the study monitor** of the event and completing the form. The form will be updated when additional information is received.

The investigator will always provide an assessment of causality at the time of the initial report as described in Section 8.7.2, "Assessment of Causality". If data obtained after reporting indicates that the assessment of causality is incorrect, then the SAE form may be appropriately amended, signed and dated, and resubmitted to the Sponsor.

In accordance with current QH guidelines, the investigator must also notify the Reviewing Ethics Committee or site governance Office of any SAEs according to the guidelines of the Ethics Committee.

## 8.6 Expeditable Events (SUSAR's)

Expeditable events are those adverse events that are **CAUSALLY** related to the study product, **AND** that are both **SERIOUS** (see Section 8.2) and **UNEXPECTED** (see Section 8.7.3). These events are deemed Suspected Unexpected Serious Adverse Reactions. Reporting timeframes to the TGA and other regulators will be conducted in accordance with the relevant guidelines.

## 8.7 Evaluating AEs and SAEs

### 8.7.1 Assessment of Intensity

The investigator will make an assessment of intensity for each AE and SAE reported during the study. The assessment will be based on the investigator's clinical judgement. The intensity of each AE and SAE recorded in the Case Report Form (CRF) will be assigned to one of the following categories:

**Mild:** An event that is easily tolerated by the Participant, causing minimal discomfort and not interfering with everyday activities.

**Moderate:** An event that is sufficiently discomforting to interfere with normal everyday activities.

**Severe:** An event which is incapacitating and prevents normal everyday activities.

An AE that is assessed as severe should not be confused with an SAE. Severity is a category utilised for rating the intensity of an event; and both AEs and SAEs can be assessed as severe. An event is defined as “serious” when it meets one of the pre-defined outcomes as described in Section 8.2 “Definition of an SAE”.

### 8.7.2 Assessment of Causality

The investigator will assess the relationship between investigational product and the occurrence of each AE/SAE. The investigator will use clinical judgment to determine the relationship. Alternative causes, such as natural history of the underlying diseases, concomitant therapy, other risk factors, and the temporal relationship of the event to the investigational product will be considered and investigated.

The causal relationship to the study product assessed by the Investigator (or medically qualified delegate) will be assessed using the following classifications:

**Not Related** In the Investigator’s opinion, there is not a causal relationship between the study product and the adverse event.

**Unlikely** The temporal association between the adverse event and study product is such that the study product is not likely to have any reasonable association with the adverse event.

**Possible** The adverse event could have been caused by the study Participant’s clinical state or the study product.

**Probable** The adverse event follows a reasonable temporal sequence from the time of study product administration, abates upon discontinuation of the study product and cannot be reasonably explained by the known characteristics of the study Participant’s clinical state.

**Definitely** The adverse event follows a reasonable temporal sequence from the time of study product administration or reappears when study product is reintroduced.

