### 1006 **9.2 Participant Withdrawal by the Investigator**

1007 Patients will be withdrawn from the study by the Investigator, prior to completion of treatment,  
1008 under the following conditions:

- 1009 • Non-compliant with study medication for seven consecutive days
- 1010 • Development of a serious adverse event assumed to be associated with the study  
1011 medication
- 1012 • Cessation of effective contraception or confirmed pregnancy
- 1013 • Continual inability to provide informed consent.

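### In section 8.7.2 the top two causality grades are misordered: plausible timing alone satisfies Definitely, so every Probable event also qualifies for it

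*Protocol*

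**What the plan says.** Protocol section 8.7.2 lists five grades in rising order: Not Related, Unlikely, Possible, Probable and Definitely. Section 8.4 has the relationship to study product documented for each adverse event.

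- **Probable** needs a reasonable temporal sequence, and the event "abates upon discontinuation of the study product and cannot be reasonably explained by the known characteristics" of the participant's clinical state. All three conditions are joined by 'and'.
- **Definitely** is worded "The adverse event follows a reasonable temporal sequence from the time of study product administration or reappears when study product is reintroduced". The two conditions are joined by 'or'.
- The rule above the grades is: "The investigator will use clinical judgment to determine the relationship". The same paragraph requires alternative causes to be considered and investigated.

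Two later rules depend on attribution, and neither names a grade. Section 8.6 begins "Expeditable events are those adverse events that are" causally related to the product, and adds that they must be both serious and unexpected. Section 9.2 lists among its grounds for withdrawal "Development of a serious adverse event assumed to be associated with the study" medication.

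**The concern.** A causality scale should ask for more evidence at each step up. Here the highest grade drops two requirements of the grade below it (abatement on stopping, and absence of another explanation) and offers recurrence only as an alternative to timing. The timing condition is also a weak filter, because section 8.1 already defines an adverse event as one temporally associated with the product.

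The consequence is grades that are unreliable at the upper end. An assessor who follows the written definition and one who relies on judgment can give the same event different grades, and section 7.5 names five sites. Any tabulation by grade, or of Probable plus Definitely, inherits this. So may the judgment of causal relatedness in section 8.6, which has no stated cut-point on the scale. A later analysis plan cannot repair grades that were collected under a faulty definition.

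**Working it through.** No sample size, power or event figure bears on this point, and the plan has no figure of its own to reproduce. The check is a truth table on the four yes/no criteria in section 8.7.2:

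- T: reasonable timing
- D: abates on discontinuation
- N: not reasonably explained by clinical state
- R: reappears on reintroduction

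Four criteria give 2 × 2 × 2 × 2 = 16 patterns. These are logical patterns and not equally likely, so the counts below are not proportions of events.

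| Definition | Rule | Patterns met |
|---|---|---|
| Probable, as written | T and D and N | 2 (R yes or no) |
| Definitely, as written | T or R | 16 − 4 = 12 |
| Definitely with 'or' changed to 'and' | T and R | 4 |
| Definitely as all Probable criteria plus recurrence | T and D and N and R | 1 |

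**As written.** Both Probable patterns have T, so both also meet Definitely: Probable lies wholly inside Definitely. The other 12 − 2 = 10 Definitely patterns fail Probable. One of them is timing only (T yes; D, N and R no). The top grade therefore has the lower bar, and the two grades are not mutually exclusive.

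**Example from the protocol.** Section 8.1 lists an acute episode of psychosis as an adverse event. Suppose one occurs on treatment with plausible timing, is explained by the underlying illness, and dosing continues. It fails Probable on D and N, fits Possible, and literally meets Definitely.

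**Which condition would do the work.** The protocol describes no reintroduction procedure, and section 7.5 bars re-entry after withdrawal. R would rarely be observed, so Definitely would rest mostly on T. Section 8.5 also requires a causality assessment at the first report of a serious event, with the form due within 24 hours of awareness. Abatement will often be unknown by then, so Probable may be unavailable while Definitely is available. The form may be amended later.

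**Effect on counts.** The protocol states no related/unrelated cut-point, so two groupings are taken as assumptions:

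- *Probable plus Definitely:* a timing-only event that belongs in Possible or lower would be added to this count.
- *Possible plus Probable plus Definitely:* moving an event among these three leaves the total unchanged. The total rises only if timing alone lifts an event out of Unlikely or Not Related.

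**Possible repairs.** Changing 'or' to 'and' removes the timing-only event but does not nest the grades, because T and R requires neither D nor N. Requiring recurrence only where re-exposure occurred would make Definitely identical to Probable whenever there was none, which is the usual case here. Requiring all four criteria leaves one pattern, inside Probable.

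**The case against.** The strongest reply is that section 8.7.2 does not ask for mechanical grading. Clinical judgment decides, and natural history, concomitant therapy and other risk factors must be considered for each event. A reasonable temporal sequence also means more than onset after a dose, since Unlikely is itself defined by timing. All of this stands as mitigation. It does not cure the wording, because the assessor must override the written definition of the top grade to reach a sensible answer.

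Other safeguards also stand. All adverse events from consent to week 14 are recorded whatever their attribution (sections 6.4.1 and 8.3), so an all-cause comparison between arms remains available. Every serious event goes to the sponsor whatever its grade (section 8.5). Study personnel and participants are blinded (section 7.7), so loose grading should not systematically favour one arm, though blinding does not make grading consistent.

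A reader might infer more than the document supports:

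- *That the whole scale is inverted.* Only the top two grades are out of order; Not Related, Unlikely and Possible are not.
- *That counts of related events will be wrong, or uninterpretable in both arms.* The protocol defines no such count, and sections 11.1 to 11.4 contain no analysis by causality. A pooled count may be unaffected, as shown above.
- *That the faulty grade determines withdrawal or expedited reporting.* Sections 9.2 and 8.6 use general wording tied to no grade, and section 8.6 also requires the event to be serious and unexpected.

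**Conclusion.** The point holds as an error in the definitions of the top two grades. On the literal wording, every Probable event qualifies as Definitely, and plausible timing alone reaches the top grade. This follows from the text and needs no outside assumption.

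The supportable consequence is that grades may be misassigned or inconsistent between assessors and sites. Counts by grade and a Probable-plus-Definitely count are exposed, and possibly the relatedness judgment in section 8.6. How many events would be affected depends on event rates and on how literally assessors read the definition, and the protocol informs neither. The error is certain but limited in reach, and it is cheap to correct.

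**What to change.** - Reword Definitely to require all the Probable criteria and documented reappearance on reintroduction. The grades are then nested, and Probable is the highest grade available without re-exposure. State that an event takes the highest grade whose criteria it fully meets, so that each event has one grade. This changes a definition only and does not call for re-exposing anyone.
- State in section 8.6 which of the five grades count as causally related.
- Re-grade, with treatment allocation still blinded, any event already graded Definitely.

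The cost is a small wording change to the protocol and CRF, some blinded re-grading if events have accrued, and a top grade that will rarely be used because the protocol describes no reintroduction.

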### 8.7.3 Assessment of Expectedness

**Expected** An adverse reaction, the nature or severity of which is consistent with the applicable product information (e.g. Investigators’ Brochure) for an unapproved medicinal product).

**Unexpected** An adverse reaction, the nature or severity of which is not consistent with information in the relevant document (e.g. Investigators’ Brochure for an unapproved medicinal product).

## 8.8 Follow-up of AEs and SAEs

All AEs and SAEs documented at a previous visit/contact and are designated as ongoing, will be reviewed at subsequent visits/contacts.

All AEs and SAEs will be followed until resolution, until the condition stabilises, until the event is otherwise explained, or until the Participant is lost to follow-up. Once resolved, the appropriate AE/SAE Case report Form (CRF) page(s) will be updated.

## **8.9 Overdose**

An overdose is defined as a dose taken by a patient in excess of the doses in the approved study protocol or available product information, either accidentally or intentionally, irrespective of whether it involves study medication or non-study medication. Overdose may be suspected or confirmed and may or may not be associated with clinical signs and symptoms.

It would definitely include (but not be limited to) those events which based on the investigators clinical judgment were considered to be of medical concern and /or require clinical observation and /or medical intervention. An overdose would include any dose greater than the highest daily dose included in the protocol or available product information. Deviations to study drug administration (i.e. resulting from poor patient compliance) which do not meet the definition of an overdose, will be recorded in the study medication compliance section of the case Report Form (CRF) and not as Serious AE's.

### **8.9.1 Reporting of Overdose**

For all overdoses the Serious AE Form will be completed and reported to the sponsor within 24 hours from the time that the Investigator or delegated research staff have been made aware of the event. See section 8.5 for all other Serious AEs. The documentation will include details of any associated signs/symptoms or if the overdose is asymptomatic, this will be stated.

## **8.10 Pregnancy**

Details of all pregnancies in participants that occur during the treatment period and the final follow-up visit will be documented and reported to the Investigator. In addition, any pregnancies brought to the attention of the Investigator after this period, and where it is known that study medication was taken at the time of conception, will also be reported.

Although pregnancies are not generally serious AE's, the Serious AE Form will be completed and forwarded to the Investigator within 24 hours. This will provide a record of the initial notification of the pregnancy.

Pregnancy is an exclusion criterion for this study, therefore, participants who become pregnant during the study should discontinue the study medication immediately and will be withdrawn from the study. The Investigator or delegated research staff will contact the participants treating Physician and inform them of the pregnancy in writing.

## **8.11 Post-study AEs and SAEs**

A post-study AE/SAE is defined as any event that occurs outside the AE/SAE detection period as defined in Section 8.3 "Time Period, Frequency, and Method of Detecting AEs and SAEs" of the protocol.

For participants that have experienced AE's and SAE's during the trial, we will follow-up until resolution and/or liaise with the treating team to optimize ongoing care as appropriate.

## **8.12 Risk Management Process**

Table 2 below details the Risk Identification, Evaluation and Management plan for this study. It will ensure that risk and uncertainty are appropriately managed for the duration of the study. The risk management process is in accordance with the NHMRC National Statement on Ethical Conduct in Research Involving Humans (2007).

**Table 2: Risk Analysis Matrix**

**Consequence**

| Likelihood     | Negligible | Minor | Moderate | Major | Extreme |
|----------------|------------|-------|----------|-------|---------|
| Almost Certain |            |       |          |       |         |
| Likely         |            |       |          |       |         |
| Possible       |            |       |          |       |         |
| Unlikely       |            |       |          |       |         |
| Rare           |            |       |          |       |         |

**Response To Risk**

|  |           |                                            |
|--|-----------|--------------------------------------------|
|  | Very High | Immediate action required                  |
|  | High      | Urgent attention or investigation required |
|  | Medium    | Require specific attention                 |
|  | Low       | Manage through routine procedures          |

**Risk Identification, Evaluation and Management Plan**

|    | Risk                                      | Description                                                                                             | Possible Effects |                |        | Risk Management strategies                                                                                                                                                                                                                                                                                                                                                                                                          |
|----|-------------------------------------------|---------------------------------------------------------------------------------------------------------|------------------|----------------|--------|-------------------------------------------------------------------------------------------------------------------------------------------------------------------------------------------------------------------------------------------------------------------------------------------------------------------------------------------------------------------------------------------------------------------------------------|
|    |                                           |                                                                                                         | Likelihood       | Consequence    | Rating |                                                                                                                                                                                                                                                                                                                                                                                                                                     |
| 1. | Psychological discomfort during interview | Participants may experience psychological discomfort when answering questions in the clinical interview | Possible         | Minor-moderate | Medium | 
The PICF clearly states the potential risk of discomfort.
 
Recruitment of experienced mental health clinicians who will be able to minimise and manage discomfort.
 
Participants will be clinically assessed at baseline, and every second week for 12 weeks. We will also contact participants once a week between face-to-face assessments by phone or other electronic means where participants are given the
 |

|    |                                             |                                                                               |          |                 |      |                                                                                                                                                                                                                                                                                                                                                                                                                                                    |
|----|---------------------------------------------|-------------------------------------------------------------------------------|----------|-----------------|------|----------------------------------------------------------------------------------------------------------------------------------------------------------------------------------------------------------------------------------------------------------------------------------------------------------------------------------------------------------------------------------------------------------------------------------------------------|
|    |                                             |                                                                               |          |                 |      | 
opportunity to discuss any concerns/discomforts re previous appointment.
 
Clinicians will direct and assist participants to gain support if required.
                                                                                                                                                                                                                                                                                 |
| 2. | Inconvenience of participating in the trial | Participants may be inconvenienced by time taken to participate in the trial. | Possible | Negligible      | Low  | 
The PICF clearly states the battery of clinical assessments to be completed and the approximate time and frequency for clinical assessment visits.
 
Participants will be given as many breaks as necessary throughout the clinical assessment visit.
 
Participants will be reimbursed for their time involved in the trial.
 
Participants will be reminded that the trial is voluntary and they can withdraw at any time.
 |
| 3. | History of self-harm/suicidal ideation      | Participant expresses suicidal ideation.                                      | Possible | Moderate-severe | High | 
Recruitment of experienced mental health clinicians who are trained in conducting risk assessment and managing high risk situations.
 
Research staff will have access to
                                                                                                                                                                                                                                                              |

|    |            |                                                                                                                                                                                   |          |            |     |                                                                                                                                                                                                                                                                                                                                                                                                                                                                                                                                                                                                                                                                                                         |
|----|------------|-----------------------------------------------------------------------------------------------------------------------------------------------------------------------------------|----------|------------|-----|---------------------------------------------------------------------------------------------------------------------------------------------------------------------------------------------------------------------------------------------------------------------------------------------------------------------------------------------------------------------------------------------------------------------------------------------------------------------------------------------------------------------------------------------------------------------------------------------------------------------------------------------------------------------------------------------------------|
|    |            |                                                                                                                                                                                   |          |            |     | 
a clinically trained senior staff including a Project Manager and Chief Investigator who will assist research staff to conduct risk assessment and implement risk management plan if required i.e. notifying treating team and assisting in the participant accessing appropriate support (e.g. emergency services)
 
Previously identified high risk patients and recent risk assessments will be discussed at weekly team meetings and their management reviewed by senior research staff (including Project Manager and Chief Investigator).
 
Research staff will be given support and feedback on risk assessments and their management to improve skills throughout the project.
 |
| 4. | Blood test | Two blood samples will be taken from participants who consent to the procedure. Participants may experience some short term mild discomfort from the blood draw. Participants may | Possible | Negligible | Low | 
The PICF clearly states the potential complications associated with the blood draws. Participants provide specific consent for this procedure which is identified on the consent form.
                                                                                                                                                                                                                                                                                                                                                                                                                                                                                                           |

|    |          |                                                                                                                             |          |                |             |                                                                                                                                                                                                                                                                                                                                                                                                                                                                                                                                                                                                                                         |
|----|----------|-----------------------------------------------------------------------------------------------------------------------------|----------|----------------|-------------|-----------------------------------------------------------------------------------------------------------------------------------------------------------------------------------------------------------------------------------------------------------------------------------------------------------------------------------------------------------------------------------------------------------------------------------------------------------------------------------------------------------------------------------------------------------------------------------------------------------------------------------------|
|    |          | experience minor complications such as local bruising and inflammation of the vein used.                                    |          |                |             | 
Participants will be taken to recognised pathologies who have trained phlebotomists to conduct the blood draws.
 
Participants are made aware they can refuse a blood draw at any stage throughout the study.
                                                                                                                                                                                                                                                                                                                                                                                                               |
| 5. | Overdose | An overdose would include any dose greater than the highest daily dose included in the protocol or prescribing information. | Possible | Minor-Moderate | Medium-High | 
For all overdoses the Serious AE Form will be completed and reported to the sponsor within 24 hours from the time that the Investigator or delegated research staff was notified of the overdose.
 
Participants will be provided with 14 days' supply (blister pack) at each face to face visit.
 
Research staff will conduct a pill count at each face to face visit.
 
Research staff will conduct medication compliance questionnaire at each face to face visit and phone contact.
 
Any identified issues with medication compliance will be discussed at weekly team meetings. Senior research staff
 |

|    |                                                       |                                                                                                                                                                                            |          |                |              |                                                                                                                                                                                                                                                                                                                                                                                                                                                                                                 |
|----|-------------------------------------------------------|--------------------------------------------------------------------------------------------------------------------------------------------------------------------------------------------|----------|----------------|--------------|-------------------------------------------------------------------------------------------------------------------------------------------------------------------------------------------------------------------------------------------------------------------------------------------------------------------------------------------------------------------------------------------------------------------------------------------------------------------------------------------------|
|    |                                                       |                                                                                                                                                                                            |          |                |              | (including Project Manager and Chief Investigator) will determine the most appropriate plan of action if required.                                                                                                                                                                                                                                                                                                                                                                              |
| 6. | Home visits                                           | Participants may be seen at home rather than in the clinic.
Individuals with psychosis can often experience hallucinations and delusions which could result in unpredictable behaviour. | Possible | Minor-Moderate | Medium-High  | 
First preference should be interview conducted at the clinic in a suitable interview room.
 
Two staff will be required for home visits and will carry a mobile phone.
 
Research staff will adhere to a sign in/out policy and advise the Project Manager of the address they will be attending.
 
Any incidents from a home visit will be reported to the Project Manager and Chief Investigator and documented in the CRF or if required reported to Metro South HREC.
 |
| 7. | Transporting participants in QLD Health work vehicles | Research staff will be transporting participants to pathology appointments and may be required to transport participants to the interview site.
- There may be risk associated with     | Possible | Minor-Moderate | Medium -High | 
Research staff will have a current QLD Driver's Licence and completed the mandatory Driver Safety E-Learning Course.
 
Recruitment of experienced mental health clinicians who will be able to and manage
                                                                                                                                                                                                                                                                           |

|  |  |                                                                                                                                                                                     |  |  |  |                                                                                                                                                                                          |
|--|--|-------------------------------------------------------------------------------------------------------------------------------------------------------------------------------------|--|--|--|------------------------------------------------------------------------------------------------------------------------------------------------------------------------------------------|
|  |  | 
motor vehicle accident
 
 
- There may be risks associated with unpredictable behaviour of a patient whilst being transported.
 
 |  |  |  | 
unpredictable behaviour.
 
Research staff will carry a mobile phone and adhere to a sign in/out policy and advise the Project Manager of the address they will be attending.
 |
|--|--|-------------------------------------------------------------------------------------------------------------------------------------------------------------------------------------|--|--|--|------------------------------------------------------------------------------------------------------------------------------------------------------------------------------------------|

999

1000  
1001  
1002

